## Abstract

**Background:**

Australia has an enviable record of safety for women in childbirth. There is nevertheless growing concern at the increasing level of intervention and consequent morbidity amongst childbearing women. Not only do interventions impact on the cost of services, they carry with them the potential for serious morbidities for mother and infant.

Models of midwifery have proliferated in an attempt to offer women less fragmented hospital care. One of these models that is gaining widespread consumer, disciplinary and political support is caseload midwifery care. Caseload midwives manage the care of approximately 35-40 a year within a small Midwifery Group Practice (usually 4-6 midwives who plan their on call and leave within the Group Practice.) We propose to compare the outcomes and costs of caseload midwifery care compared to standard or routine hospital care through a randomised controlled trial.

**Methods/design:**

A two-arm RCT design will be used. Women will be recruited from tertiary women's hospitals in Sydney and Brisbane, Australia. Women allocated to the caseload intervention will receive care from a named caseload midwife within a Midwifery Group Practice. Control women will be allocated to standard or routine hospital care. Women allocated to standard care will receive their care from hospital rostered midwives, public hospital obstetric care and community based general medical practitioner care. All midwives will collaborate with obstetricians and other health professionals as necessary according to the woman's needs.

**Discussion:**

Data will be collected at recruitment, 36 weeks antenatally, six weeks and six months postpartum by web based or postal survey. With 750 women or more in each of the intervention and control arms the study is powered (based on 80% power; alpha 0.05) to detect a difference in caesarean section rates of 29.4 to 22.9%; instrumental birth rates from 11.0% to 6.8%; and rates of admission to neonatal intensive care of all neonates from 9.9% to 5.8% (requires 721 in each arm). The study is not powered to detect infant or maternal mortality, however all deaths will be reported. Other significant findings will be reported, including a comprehensive process and economic evaluation.

**Trial registration:**

Australian New Zealand Clinical Trials Registry ACTRN12609000349246

## Background

Australia has an enviable record of safety for women in childbirth [1]. There is nevertheless growing concern at the increasing level of intervention, cost and consequent morbidity amongst childbearing women [2]. Rising intervention rates are most clearly reflected in the changes in rates of caesarean section which have increased over time. In 1991, only 19.0% of births were via caesarean section. By 2006, 31% of all births were via caesarean [1]. In addition to caesarean section, population based research in Australia revealed that amongst women with uncomplicated pregnancies, a third of all women currently have some form of intervention such as an induction or augmentation of their labour combined with an epidural [3]. Cost modelling of these interventions showed a relative cost increase of up to 50% for low risk primiparous women and up to 36% for low risk multiparous women as labour interventions accumulated [4].

Not only do interventions impact on the cost of services, they carry with them the potential for serious morbidities for mother and infant. Over a decade ago a large population based study in Victoria found that more than nine out of ten women had at least one significant medical complaint after giving birth [5]. Compared with spontaneous vaginal births, women having an instrumental birth had increased odds for perineal pain (OR 4.69, 95%CI 3.2-6.8) sexual problems (OR 2.06, 95% CI 1.4-3.0), and urinary incontinence (OR 1.81, 95% CI 1.1-2.91) [5]. Other studies have shown that a first birth by forceps delivery can cause a twofold increase in the risk of having persistent faecal incontinence, and in about half these cases faecal incontinence may persist for at least five years [6]. Caesarean births carry the risk of increased perinatal mortality in subsequent pregnancies[1,7,8] and the risk of morbidity associated with surgery[9] and possible maternal complications in subsequent pregnancies (e.g., uterine rupture, placenta praevia, and placenta accreta) [10,11]. Operative birth also increases the fetal risks of respiratory distress syndrome [12] persistent pulmonary hypertension,[13] and admission to special care or neonatal intensive care nurseries particularly if the caesarean section is performed before the onset of labour [12,14,15]. Australian research into the rates of admission to neonatal intensive care of term babies of low risk women found the overall rate of admission is currently as high as 7.32% amongst low risk women [15].

An intervention that could lower rates of caesarean section, instrumental birth and epidural analgesia with no increase in mortality or morbidity for the mother or baby would improve the quality of maternity care, reduce unnecessary or harmful interventions and be cost effective.

No intervention reported in the Cochrane Library of systematic reviews of pregnancy and childbirth has had a more significant effect on lowering rates of intervention during childbirth than 'continuity of care' [16]. However, in Australia at present fewer than10% of women have access to continuity of care [17] and some women may meet up to 20 different midwives or caregivers from the time they begin antenatal care until the baby is born and the mother is discharged from postnatal care. Models of midwifery have proliferated in an attempt to offer women more continuity of care. We proposed to compare the outcomes and costs of caseload midwifery care compared to standard or routine hospital care for childbearing women through a randomised controlled trial.

### Caseload midwifery

The aim of caseload midwifery is to provide women with the same midwife (or small group practice of midwives) to look after them from booking in through until the time they are discharged from care at about four to six weeks following the birth of the baby.

Despite the substantial health care costs associated with maternal and infant health, there are minimal data on the cost effectiveness of maternity care offered in the public (or private sector) in Australia. Allocating finite resources in ways that are most effective in improving health outcomes continues to be a challenge [18]. As yet there is no cost benefit analysis of the caseload midwifery model for women of all risk anywhere in the world.

There remains continuing uncertainty and debate about the risks, benefits and costs of midwifery led models versus other models of maternity care [16,19,20]. Several large national reviews [17,21] and a workforce study [22] identified that the current limited and inflexible scope of practice negatively affects Australian midwives' sense of satisfaction with their employment. The Commonwealth Health Workforce Review [23] found that workforce shortages, inflexibilities and inefficiencies in workplace arrangements are major contributors to poor health outcomes.

We plan to implement and evaluate Midwifery Group Practices at two large teaching maternity hospitals in Australia to compare the outcomes and costs of caseload midwifery care and standard or routine hospital care for childbearing women.

Ethical approval and site specific ethical approval was received from all University and Area Health Service Human Research Ethics Committees governing the study sites: University of Sydney HREC approval REF NO 12068; Lead HREC approval REF NO 0805072M.

## Methods/design

The study uses a pragmatic two arm, unblinded randomised controlled design, to compare caseload midwifery care with standard maternity care.

### Aims and Objectives

The aim of the study is to compare the outcomes and costs of caseload midwifery care compared to standard or routine hospital care for childbearing women through a randomised controlled trial.

**Primary objectives **are to determine whether women receiving caseload midwifery care experience the same rates of caesarean section, instrumental births and use of epidural analgesia compared to women receiving routine care and to determine whether women with identified risk factors at the onset of labour experience the same rates of neonatal morbidity (including admission to the neonatal intensive care unit), and perinatal mortality compared to routine care.

We will determine whether caseload midwifery care costs the same as routine maternity care and whether women who receive caseload care experience the same potential benefits and consequences of postnatal care as women receiving routine maternity care.

**Secondary objectives **are to determine whether midwives offering caseload practice experience the same levels of work satisfaction and the same levels of productivity as midwives working in conventional rostered and rotating shifts; and to determine whether obstetricians working with caseload midwives experience the same levels of professional satisfaction as obstetricians working with rostered midwives in the routine work setting. We will also determine the rates of postnatal depression and smoking in pregnancy.

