### Outcome measures

The *primary maternal outcomes *of the study are the proportion of women in each arm of the study:

• having caesarean section operations,

• instrumental births

• spontaneous vaginal births

• epidural analgesia for labour and birth

The *primary neonatal outcomes *of the study are the proportion of infants in each arm of the study who have:

• Apgar scores less than or equal to 7 at 5 minutes

• preterm birth (less than 37 completed weeks)

• admission to special care nursery or neonatal intensive care unit;

*Secondary maternal outcomes *include the proportion of women in each arm of the study who have:

• antenatal admissions

• induction and/or augmentation of labour

• women who are breastfeeding at six weeks and six months

*Cost outcomes *include:

• Comparative average cost per mother and baby episode as an AR-DRG

In addition to the primary outcomes listed above we will report on

*Other neonatal outcomes *including: low birth weight (less than 2500 g); length of neonatal hospital stay; neonatal convulsions; neonatal trauma (fracture or palsies); neonatal resuscitation: use of neonatal respiratory support (mechanical ventilation/CPAP) and/or perinatal mortality.

*Other maternal outcomes *include the rate of maternal complications (e.g. hypertension, ante partum haemorrhage, cord prolapse etc) and miscarriages in both the intervention and control arms; the proportion of women who have perineal trauma (episiotomy, 1st, 2nd, 3rd or 4th degree perineal tear, sutures required); postpartum haemorrhage (more than 500 ml or any amount which causes deterioration in maternal health; and/or blood transfusion); and serious maternal complications (e.g. intensive care unit admission or death).

*Although the study is not powered to detect other related outcomes including measures of perinatal mortality (e.g. fetal or neonatal death,) or maternal mortality, these events will be reported in full*.

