### Study Power

With 750 women or more in each of the intervention and control arms the study is powered (based on 80% power; alpha 0.05) to detect a difference in caesarean section rates of 29.4 to 22.9%; instrumental birth rates from 11.0% to 6.8%; and rates of admission to neonatal intensive care of all neonates from 9.9% to 5.8% (requires 721 in each arm). The study is not powered to detect infant or maternal mortality, however all deaths will be reported. Secondary outcomes will include rates of smoking cessation (eg 14.8% to 9.9% needing 747 women in each arm) and breastfeeding initiation and duration. We have calculated a sample to include a 30% attrition rate; therefore we aim to recruit a total of 1,950 women. All outcome measures identified by the Cochrane Protocol [19] will be collected. Individual hospital data bases and a purposefully designed data base will collect all primary and secondary outcome and process measures in addition to most cost outcome measures.

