## Discussion

This trial will provide a comprehensive and rigorous evaluation of caseload midwifery maternity care. The evidence that this trial can provide is long overdue for maternity policy makers and service providers who are responsible for the effective design, delivery and costs of services that are the most frequent cause of hospitalisation in Australia today.

Restructuring maternity services to introduce caseload midwifery care involves radical changes to conventional or routine midwifery and obstetric practices [29-31]. All these changes make an impact on health planning and the allocation of finite resources [18]. Many innovations are introduced in a relative policy vacuum. Models of maternity care are no exception. This proposed trial is significantly innovative because it is designed to be undertaken on as a multisite study in two different states within Australia and includes women of *all risk *rather than *low **risk *women. Because our proposed trial meets the criteria of the Cochrane Systematic Review of midwifery caseload care in methods; randomisation; definitions of the intervention and control arms; outcome measures and statistical analysis,[19] the results will contribute to a wider inquiry and meta-analysis in the future.

In addition to evidence on the experiences of women receiving caseload midwifery care and the experiences of obstetricians and midwives offering caseload care, the outcomes of the proposed trial will contribute:

1. Level 1 evidence of the safety and effectiveness of having a known caseload midwife for the continuum of pregnancy birth and postnatally.

2. Level 1 evidence of the safety and effectiveness of caseload midwifery care for women of all risk.

3. Level 1 evidence on the cost effectiveness of caseload midwifery care and routine obstetric care for all women.

4. 'Australian randomised controlled trial data to the Cochrane systematic review of midwife led care[19].

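### Perinatal mortality sits in a primary objective about sameness that the protocol says it is not powered to answer, and the sameness wording in general does not fit a trial sized for differences

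*Protocol article*

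**What the plan says.** Aims and Objectives, in the protocol article, sets the first primary objective as "to determine whether women receiving caseload midwifery care experience the same rates of caesarean section, instrumental births and use of epidural analgesia". The second asks whether "women with identified risk factors at the onset of labour experience the same rates of neonatal morbidity", and closes with "and perinatal mortality compared to routine care". A separate paragraph, labelled neither primary nor secondary, adds "We will determine whether caseload midwifery care costs the same as routine maternity care".

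Study Power describes a different kind of question: with 750 or more women per arm, "the study is powered (based on 80% power; alpha 0.05) to detect a difference in caesarean section rates of 29.4 to 22.9"%. It gives matching pairs for instrumental birth (11.0% to 6.8%) and for neonatal intensive care admission among all neonates (9.9% to 5.8%, 721 per arm). Epidural and cost are not sized. Analysis plans chi-squared tests and t-tests, with relative risks and 95% confidence intervals for the primary outcomes. The article gives no equivalence or non-inferiority margin.

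On perinatal mortality, Outcome measures places it among the other neonatal outcomes and says: "Although the study is not powered to detect other related outcomes including measures of perinatal mortality". The Abstract and Study Power also say that the trial is not powered for infant or maternal mortality. The Discussion nevertheless lists among the trial's contributions "Level 1 evidence of the safety and effectiveness of caseload midwifery care for women of all risk".

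**The concern.** Two things do not fit together.

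The narrower one is a contradiction on perinatal mortality. It belongs to a primary objective in one section, is an other outcome in the next, and is disclaimed for power in both Outcome measures and Study Power, while the Discussion announces evidence of safety. An analysis plan written later cannot repair a primary objective that its own protocol says the trial is not sized to answer.

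The broader one is the wording of the objectives. A test of difference can show that rates are not the same. It cannot show that they are, unless a margin says how close is close enough. Read literally, the objectives could be answered affirmatively only by treating non-significance as agreement. At stake is what may be concluded from a null or inconclusive result, above all on harm to infants of higher-risk women.

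**Working it through.** **1. The plan's own figure.** Inputs from Study Power: 80% power, alpha 0.05 (taken as two-sided), equal arms. Formula:

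n = [1.96·√(2p̄(1−p̄)) + 0.842·√(p₁(1−p₁) + p₂(1−p₂))]² / δ², then the continuity correction n·[1 + √(1 + 4/(nδ))]²/4.

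Caesarean section: p₁ = 0.294, p₂ = 0.229, p̄ = 0.2615, δ = 0.065. The first step gives 717 and the correction gives 747. The same route gives 768 for instrumental birth, 723 for neonatal intensive care admission (stated 721) and 747 for smoking (stated 747). A one-sided calculation gives 595 for caesarean section and does not reproduce the plan. So 750 per arm is a two-sided test-of-difference calculation with no margin in it. I find no arithmetic error in it.

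**2. What equal observed rates would leave open.** 95% interval for the relative risk: exp(±1.96·√(2(1−p)/(np))), n = 750 per arm.

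- Caesarean section, p = 0.294: √(1.412/220.5) = 0.080, interval 0.85 to 1.17.
- Instrumental birth, p = 0.11: √(1.78/82.5) = 0.147, interval 0.75 to 1.33.
- Neonatal admission, p = 0.099: √(1.802/74.25) = 0.156, interval 0.74 to 1.36.

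**3. The margin that 750 per arm could support.** Two one-sided 0.05 tests, equal true rates, 80% power: margin = (1.645 + 1.282)·√(2p(1−p)/750). This gives about 6.9 points for caesarean section, 4.7 for instrumental birth and 4.5 for neonatal admission. The differences the trial is designed to find are 6.5, 4.2 and 4.1 points (29.4 − 22.9, 11.0 − 6.8, 9.9 − 5.8). The trial could therefore show equivalence only within margins wider than the effects it regards as worth detecting. Conversely, true effects half the design size would be significant only 27% to 29% of the time, and a true 2-point rise in neonatal admission only 24% of the time.

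**4. Perinatal mortality.** The article gives no rate, so I assume control rates of 0.5%, 1.0% and 1.5%. The interval formula in step 2, with n = 750, gives:

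- 0.5%: √(1.99/3.75) = 0.728, interval 0.24 to 4.2; power to detect a doubling 20%.
- 1.0%: √(1.98/7.5) = 0.514, interval 0.37 to 2.7; power 36%.
- 1.5%: √(1.97/11.25) = 0.418, interval 0.44 to 2.3; power 50%.

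**5. The subset that the objective names.** The neonatal objective concerns women with risk factors at labour onset, not all women. The article does not give their share. If it were half (375 per arm, assumed), the 1.0% case would become √(1.98/3.75) = 0.727, interval 0.24 to 4.2, and power to detect a doubling would be 12%, 20% and 28% at the three rates. Neonatal admission is sized on all neonates. With the same 9.9% and 5.8% (assumed to apply in the subset), power would be 37%, 55% or 70% if the subset were 30%, 50% or 70% of women.

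**The case against.** The best reply is that the sameness wording is only a null hypothesis put as a question. It is used for every comparative objective, including staff satisfaction and productivity, and the answer may be no. The overall aim is to compare outcomes and costs, the Background speaks of an intervention that could lower intervention rates, and the sizing and tests look for differences. For caesarean section, instrumental birth and epidural this largely stands: the design is coherent and only the phrasing is loose.

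A reader might go further and infer that the investigators intend to report non-significance as sameness or safety. The article does not say so. Relative risks with 95% intervals would show what has not been excluded. The lack of power for mortality is disclosed openly, deaths will be reported in full, and a committee blinded to allocation reviews all perinatal deaths. A reader might also count cost as a primary objective, but it carries no such label and has its own outcome heading. Finally, Level 1 may be meant as a grade of study design rather than a promise to show absence of harm.

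This does not dispose of the mortality point. The Background's hoped-for result includes no increase in mortality or morbidity, which is a no-harm claim and not a difference claim. The intervals are promised for primary outcomes, and perinatal mortality is not on that list. However Level 1 is meant, the word safety stands beside an outcome for which the trial disclaims power.

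**Conclusion.** The point holds in two parts of unequal weight. The firm part is the inconsistency on perinatal mortality: a primary objective of sameness in a risk-factor subset, an outcome classed as other, an admitted lack of power, no margin, and a safety claim in the Discussion. Equal observed rates would still leave roughly a doubling to a quadrupling of risk unexcluded (upper limits 2.3 to 4.2) with all 750 women per arm, and more in the subset. These figures rest on assumed control rates of 0.5% to 1.5%.

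The lesser part is the wording of the remaining objectives. A non-significant result could not answer them as literally phrased, since neonatal admission up to 36% higher in relative terms would remain compatible with equal observed rates. This is a mismatch of wording with design, not evidence of a planned misinterpretation. The sample-size calculation is not in question.

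**What to change.** - In Aims and Objectives, ask whether rates *differ* for caesarean section, instrumental birth, epidural, and neonatal morbidity including neonatal admission. A non-directional verb suits the planned two-sided tests. Note there that epidural is not sized in Study Power, and that neonatal admission is sized on all neonates and not on women with risk factors.
- Take perinatal mortality out of the primary objective, in line with Outcome measures, and report it descriptively with a 95% confidence interval.
- State that a non-significant difference will not be reported as sameness or as safety. Put generally, this also covers the cost objective.
- In the Discussion, limit the safety claim to what the confidence intervals exclude.

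The cost is wording only: sample size, tests and data collection stay as they are. The trial gives up a safety-equivalence claim that it could not have supported.

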### Outcome measures

The *primary maternal outcomes *of the study are the proportion of women in each arm of the study:

• having caesarean section operations,

• instrumental births

• spontaneous vaginal births

• epidural analgesia for labour and birth

The *primary neonatal outcomes *of the study are the proportion of infants in each arm of the study who have:

• Apgar scores less than or equal to 7 at 5 minutes

• preterm birth (less than 37 completed weeks)

• admission to special care nursery or neonatal intensive care unit;

*Secondary maternal outcomes *include the proportion of women in each arm of the study who have:

• antenatal admissions

• induction and/or augmentation of labour

• women who are breastfeeding at six weeks and six months

*Cost outcomes *include:

• Comparative average cost per mother and baby episode as an AR-DRG

In addition to the primary outcomes listed above we will report on

*Other neonatal outcomes *including: low birth weight (less than 2500 g); length of neonatal hospital stay; neonatal convulsions; neonatal trauma (fracture or palsies); neonatal resuscitation: use of neonatal respiratory support (mechanical ventilation/CPAP) and/or perinatal mortality.

*Other maternal outcomes *include the rate of maternal complications (e.g. hypertension, ante partum haemorrhage, cord prolapse etc) and miscarriages in both the intervention and control arms; the proportion of women who have perineal trauma (episiotomy, 1st, 2nd, 3rd or 4th degree perineal tear, sutures required); postpartum haemorrhage (more than 500 ml or any amount which causes deterioration in maternal health; and/or blood transfusion); and serious maternal complications (e.g. intensive care unit admission or death).

*Although the study is not powered to detect other related outcomes including measures of perinatal mortality (e.g. fetal or neonatal death,) or maternal mortality, these events will be reported in full*.

